Appendix 1 Water Delivery Process

**STUDY PROTOCOL**

# 1. BACKGROUND AND RATIONALE

#### General Introduction

*Study summary*

This study evaluates the efficacy of ELO water as an adjuvant modality in diabetes care for enhancement of glycemic control in patients with Type 2 diabetes mellitus.

##### *Diabetes – a major public health problem*

Global diabetes mellitus prevalence is at a staggering rate. The IDF reported that in 2015, a total of 415 million people suffer from diabetes and by 2040, this number is expected to rise to 642 million^1^. Out of the current 415 million people with diabetes, 320 million belong to the economically active age group of 20 -64 years^1^.

In 2015, IDF reported that Singapore has 12.8% of its population diagnosed with diabetes mellitus, a similar percentage as reported in the USA^1^. More than 90 percent are type 2 diabetes, which is generally considered to be contributed largely by lifestyle. Our Minister of Health has recently declared war on diabetes because the socioeconomic impact of diabetes on Singapore is monumental and is expected to escalate in the coming years.

##### *Diabetes management principles*

A prime care parameter that influences risks of diabetic complications is blood glucose control. Landmark studies such as the UK Prospective Diabetes Study (UKPDS)^2^ and Diabetes Control and Complications Trial(DCCT)^3^ have established that glycemic reduction holds the key to reducing risks of diabetic complications. As type 2 diabetes mellitus is a long term condition with a significant lifestyle component in its management, it stands to reason that finding effective lifestyle interventions to support drug therapy will help improve diabetes control. If there are lifestyle measures that are safe, convenient and form a part of normal living that can assist a diabetes patient in reducing blood glucose levels, these should be investigated as a potential aid in diabetes care.

##### *Oxygen, water and diabetes*

Oxygen is critically required by living cells. Water is equally important for cell survival. Hypoxia(lack of oxygen) and dehydration(lack of water) deprives cells of basic needs for oxygen and water and can lead to cell dysfunction and disease.

Oxygen improves the energy economics of the cell significantly. When cells are in a hypoxic environment, anaerobic processes are utilised by the cells to generate energy. The energy generating pathway under hypoxia produces only 2-4 ATP per molecule of glucose^4^. On the other hand, when oxygen is available to the cells, glucose is channelled into the mitochondria for oxidative phosphorylation and the electron transfer chain so that one molecule of glucose produces 32-36 ATP^4^.Oxygen vitally affects every cell type of the human body because every cell requires oxygen for energy generation to meet its metabolic needs.

A study done by researchers from Harvard Medical School, Ikazia Hospital, Rotterdam and Erasmus MC–University Medical Center, Rotterdam which was published in the Journal of Vascular Surgery demonstrated that diabetes patients (both type 1 and type 2) had 10 - 15% lower tissue oxygenation using transcutaneous oxygen (TcPO2) values obtained on the chest wall and limbs^5^. The study concluded that diabetes patients without signs of peripheral disease or neuropathy had significantly lower TcPO2 values compared with age- and sexmatched non diabetic patients^4^.*In vitro* studies on hypoxia has shown that that hypoxia creates a state of insulin resistance in fat cells through HIF (Hypoxia Inducible Factor) transcription factor expression^6^. Hypoxia could be mechanistic in creating insulin resistance in adipose tissue of diabetes or obese patients. A human trial by the University of Adelaide investigated the effect of increased tissue oxygenation on insulin sensitivity using the HOMA-IR method of euglycemic insulin clamp studies. This study found that when type 2 diabetes patients and overweight non diabetic patients were placed in a hyperbaric oxygen chamber, their insulin sensitivity improved^7^. Taken together, these studies suggest that there is a pathophysiological link between tissue oxygen levels and diabetes, possibly through mechanisms that involve insulin signalling and insulin resistance.

Cell processes occur in a ‘watery’ environment because 70 percent of cells is made of water. Within the living cells, water is used as a carrier of nutrients, electrolytes and oxygen for cell processes such as energy production, protein production and waste management.

Dehydration is a feature in poorly controlled diabetes and can aggravate hyperglycemia^8^ (high blood glucose) in diabetes patients. Chronic dehydration has been implicated as a factor in development of renal disorders including diabetic nephropathy^8^.A review published in the American Journal of Nephrology found that reducing vasopressin secretion, increasing water intake may have a beneficial effect on renal function in patients with all forms of chronic kidney disease (CKD) and may also benefit those at risk ofCKD^10^.The effects of good hydration on renal function of Type 2 diabetes patients should be explored as a simple lifestyle measure that could help ameliorate diabetic nephropathy.

*ELO water – what is it?*

ELO water is a pure drinking water that is enriched with molecular oxygen in a stable form. The ELO water looks and tastes like good quality drinking water without unusual taste or colour. It has passed the AVA standards for drinking water in terms of purity and mineral content and has been on sale commercially in Singapore since November 2015.

Oxygen naturally has low water solubility and has a tendency to immediately escape back into the air from solution. A special proprietary technology, the result of joint technology efforts by Hyflux Ltd and Kagun Europe Zrt Hungary, is able to produce ELO Water with a stable oxygen-enrichment. The oxygen content of ELO water is stable and is between 15 to 19 ppm, much higher than oxygen content in tap water (3-7 ppm)

A study by Ugolev has demonstrated that the mammalian gut lining is capable of oxygen absorption when his study demonstrated that oxygen saturated saline had 50-80% of the dissolved oxygen content absorbed when it was passed through 15 cm of rat gut^10^. Providing both hydration and oxygen, ELO water is an interesting type of water which potentially presents another platform to deliver oxygen and hydration which should be explored.

##### *Hypoxia Inducible Factor -1 alpha (HIF-1* α*)*

Systemic tissue hypoxia has been associated with increased plasma levels of HIF-

1α (Hypoxia Inducible Factor)^12^. In normoxic tissue conditions, HIF-1α is rapidly and continuously degraded following translation. Tissue hypoxia, however, induces a sustained increase in the expression of HIF-1α, measurable as plasma HIF-1α. This is mainly due to oxygen-dependent hydroxylation of HIF-1α amino acid proline residues in a reaction catalyzed by HIF prolyl-4-hydroxylases in the presence of its cofactors, oxygen and 2-oxoglutarate^13^. In human trials, it is technically more challenging to use PET scan and hypoxia radiotracers to establish change in tissue hypoxia levels, hence, we will be monitoring the plasma HIF-1α as an indication of systemic tissue hypoxia. This marker would indirectly help us monitor the effect of ELO water on the state of tissue oxygenation.

##### *Long chain acylcarnitines (LCAC)*

Diabetes patients and obese individuals have been observed to show higher plasma levels of long chain acyl-carnitines (LCAC).^14^Long chain acyl-carnitines are produced when there is incomplete mitochondrial fatty acid beta-oxidation (FAO) and this has been observed in diabetes patients. There are studies suggesting the role of LCAC in insulin signaling interference^15^, a potential mechanism for insulin resistance. Hypoxia itself has been shown to be associated with insulin resistance in adpocytes^5^. In a study involving dog muscle cells, hypoxia produced an accumulation of long chain acylcarnitines in the muscle cells^16^. It is possible that reversing tissue hypoxia in diabetes patients could enable the cellular mitochondria to completely breakdown long chainfatty acids through complete beta-oxidation and improve insulin resistance.

### 1.1. Rationale and justification for the Study

## a. Rationale for the Study Purpose

This study seeks to find a way to help diabetes patients obtain better glycemic control through drinking ELO water as part of the lifestyle intervention in diabetes care.

It is possible that orally taking in the oxygen carried in ELO water on a regular basis can supplement the conventional channel of oxygenation through the lungs and enhance oxygen availability to the cellular mitochondria. The hypoxia pathway to LCAC accumulation may be reduced using ELO water.^16^This could potentially improve fatty acid beta oxidation occurring in the mitochondria and reduce accumulation of long chain acylcarnitines (LCAC) in the plasma, which has been associated with interference with proper insulin signalling and increased insulin resistance^14,15^.

## b. Rationale for Doses Selected

It is suggested that 1.5 litres (1 bottle) of ELO water is to be consumed every day for a period of 24 weeks. Other forms of water must be used to supplement this in order to achieve the 2-3 litre total daily requirement of water in an adult.

24 weeks of daily ELO water consumption is a long enough period to ascertain changes in HbA1c.

## c. Rationale for Study Population

Rationale for inclusion criteria:

- The target population is adult Type 2 diabetes mellitus patients with HbA1c of between 8.0 – 11% in the 6 months prior to recruitment.

- The patients with this range of HbA1c have suboptimal glycemic control and allows the study to ascertain glycemic improvements.

Rational for exclusion criteria:

- Patients with comorbidities that require fluid restriction e.g. heart failure, renal failure are not suitable for studies that require oral fluid consumption of at least 1.5 litres per day.

- Pregnant patients are excluded from this study because at different stages of pregnancy, their insulin sensitivity changes.

## d. Rationale for Study Design

The study is a double-blinded, randomised and controlled trial (RCT) with 2 study arms, i.e. the ELO water arm versus the control arm with placebo drinking water. The control arm with placebo drinking water will define the biological effects attributable to ELO water with its higher oxygen content as opposed to effects due to general hydration. Blinding the patients to the type of water consumed will ensure that placebo effects are removed. The study investigators are also blinded to the type of water the patient is consuming to avoid study biases. The patients are asked to keep a water consumption diary as a way to improve monitoring of water drinking compliance.

# 2. HYPOTHESIS AND OBJECTIVES

### 2.1. Hypothesis

Main Hypothesis

**Hypothesis 1**: ELO water as an adjuvant lifestyle intervention in Type 2 diabetes patients can improve glycemic control.

Secondary hypotheses

**Hypothesis 2:** ELO water, through its reversal of tissue hypoxia, is able to enhance mitochondrial beta oxidation of fatty acids, leading to reduced plasma levels of long chain acylcarnitines.

**Hypothesis 3:** ELO water, through a combined effect of hydration and oxygenation, is able to improve albuminuria in Type 2 diabetes patients better than hydration with regular water.

### 2.2. Primary Objectives

To evaluate oxygen-enriched ELO water as a viable aid for glycemic control when used as part of lifestyle management for Type 2 diabetes patients.

### 2.3. Secondary Objectives

1. To study the effect of drinking oxygen-enriched ELO water on mitochondrial fatty acid oxidation.
2. To study the effect of drinking oxygen-enriched ELO water on diabetic nephropathy.

### 2.4. Potential Risks and benefits:

## a. End Points – Efficacy

Primary end-point:

To achieve a reduction in HbA1c of at least 0.5% in 24 weeks

Secondary endpoints include the following:

1. Reduction in fasting blood glucose by at least 2 mmol/L
2. Reduction in fasting C14 or C16 or C18 long chain acyl carnitine by 25%
3. Reduction in any abnormally raised liver enzymes (GGT, ALT, AST) by more than 30%^17^
4. Reduction in calculated eGFR by 15 mL/min/1.73m^2^
5. Reduction in urine ACR in macroalbuminuric patients (urine ACR > 300 mg/g) of at least 48%^18^.

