###### Table 1: Trial schedule

| **Week** | **0** | **6** (+/– 1 week) | **12**  (+/– 1 week) | **24**  (+/– 1 week) |
| --- | --- | --- | --- | --- |
| Consent taking | **X** |  |  |  |
| Inclusion &  Exclusion Criteria  Check | **X** |  |  |  |
| CGH clinic review^a^ | **X** | **X** | **X** | **X** |
| Vital Signs (BP) | **X** | **X** | **X** | **X** |
| Height and Weight | **X** | **X** | **X** | **X** |
| Blood and Urine tests^b^ | **X** | **X** | **X** | **X** |
| Completion of study |  |  |  | **X** |

*a :CGH review will be performed on Week 0, 6, 12, 24 and whenever there is any adverse events. Review will include review of water diary and to ask patient whether there has been any adverse effect, and / or changes in medications, diet and physical activities*

*b: Blood and Urine tests for HbA1c, Haemoglobin, Liver function test (ALT, AST, GGT), Serum creatinine and calculated eGFR, Fasting Lipid profile – Triglyceride, Total Cholesterol, LDL, HDL, Fasting plasma glucose, Plasma Hypoxia inducible factor HIF-1α, Long chain acyl carnitine (C16) and Urine ACR*

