###### Table 3: Laboratory Test at Week 0, 6, 12, 24 weeks

| **Test** | **Collection Tube** | **Volume** |
| --- | --- | --- |
| HbA1c | K^2^EDTA Tube | 2mls |
| Hb |  |  |
| Liver function test (ALT, AST, GGT) | SST Tube with clot activator | 5mls |
| Serum creatinine and calculated eGFR |  |  |
| Fasting Lipid profile – TG, TChol, LDL, HDL |  |  |
| Fasting plasma glucose |  |  |
| Plasma Hypoxia inducible factor HIF-1α | Lithium Heparinised Tube | 8-10mls |
| Long chained acyl carnitine | Lithium Heparinised Tube | 8-10mls |
| Urine ACR | Urine Collection Bottle | At least 10mls |

Special laboratory tests used in the study

1. Plasma HIF-1α

This will be done using an ELISA based test kit from ThermoFischer

Scientific.The Thermo Scientific™ HIF-1 Alpha ELISA Kit measures human hypoxia-inducible factor 1-alpha (HIF1A) protein in plasma using the quantitative sandwich ELISA method. HIF1A standards and samples are captured by a polyclonal HIF1A antibody on the precoated plate and detected using a biotinylated monoclonal HIF1A antibody reactive to epitopes other than the capture antibody. The biotinylated detection antibody is then bound to streptavidin-HRP, which catalyzes the conversion of TMB to a colored derivative. olour development is linear for the assay’s dynamic range and directly proportional to the amount of HIF1A present in the sample.

1. Plasma acyl carnitine assay

The plasma level of acylcarnitines of various carbon lengths will be measured using tandem mass spectrometry.

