# 11. SAMPLE SIZE AND STATISTICAL METHODS

### 11.1. Determination of Sample Size

We expect there is a medium effect size ( ohen’s d = 0.5) between ELO water arm and control water arm. The minimum number subjects to be recruited into each arm will be 65 subjects (total 130 subjects) for the study to have 80% power with significance level of 5%. Taking into account a potential dropout rate of 15%, we aim to recruit 75 patients in each arm (total 150 subjects).

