### 11.2. Statistical and Analytical Plans

Categorical data will be presented as frequency (percentage). Continuous data will be presented as mean (SD), unless specified otherwise. The differences in characteristics will be examined using Chi-Square test or Fisher’s Exact test for categorical variables, and 2-sample t-test or Mann Whitney U test for continuous variables. For repeated measures variables, mixed models analysis will be used to account for drop-outs.

A two tailed, p-value of <0.05 was considered statistically significant. Statistical analysis will be performed with SPSS statistical software, version 19.0 (IBM Corp. Armonk, NY).

A statistical analysis for month 3 data is planned in order to study the short term outcomes.

This RCT will be analysed by both intention-to-treat (ITT) and per protocol (PP) approach. Patients’ non-compliance will be monitored via their water diary. The compliance rate will then be adjusted in the data analysis.

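### The only endpoint for Hypothesis 2 can be met by C14, C16 or C18, while Table 1 names C16 alone and no rule says how the alternatives are tested

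*Protocol*

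**What the plan says.** Four parts of the protocol bear on this endpoint.

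- **Section 2.1, Hypothesis 2** concerns the class and names no chain length: "leading to reduced plasma levels of long chain acylcarnitines".
- **Section 2.4.a, secondary endpoint 2** offers three alternatives: "Reduction in fasting C14 or C16 or C18 long chain acyl carnitine by 25" per cent.
- **Section 4, Table 1, footnote b** lists one analyte among the scheduled tests: "Long chain acyl carnitine (C16) and Urine ACR".
- **Section 5, Table 3** has the entry "Long chained acyl carnitine" with no chain length. The note below it says: "The plasma level of acylcarnitines of various carbon lengths will be measured using tandem mass spectrometry".

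For testing, section 11.2 gives one general rule, "A two tailed, p-value of <0.05 was considered statistically significant", and states no adjustment. It assigns no specific test to this endpoint. No section says whether the 25% fall is a result for an arm or for a patient.

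**The concern.** Hypothesis 2 is the protocol's mechanistic claim, and this is the only listed endpoint that addresses it. As written, the endpoint is one marker in one place, three alternatives in another and an open set in a third. Success could be claimed on whichever chain length happened to move, and the protocol would not contradict the claim.

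The consequence depends on what the 25% applies to. Three separate between-arm tests with an any-one rule raise the false-positive rate above the stated 5%. A single per-patient rule does not, but it counts more patients as responders when nothing has changed, and it discards information that a continuous analysis would keep.

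**Working it through.** **Plan's own figure.** Section 11.1 assumes d = 0.5 "for the study to have 80% power with significance level of 5" per cent and states 65 per arm. The normal formula gives n = 2 × (1.96 + 0.84)² / 0.5² = 62.7, so 63. The t-test gives 63.8, so 64. At 65 per arm the t-test power is 80.8%. The stated figure reproduces and this point does not affect it. Section 11.1 does not tie d = 0.5 to any endpoint; applying it to acylcarnitines below is an assumption.

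**Reading A: three between-arm tests, any one suffices.** Under independence the error is 1 − 0.95³ = 14.3%. Counting only false claims of reduction, it is 1 − 0.975³ = 7.3%. The protocol gives no correlation between the markers, so a range was simulated with three equally correlated normal test statistics:

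| Assumed correlation | Any false positive | False reduction |
|---|---|---|
| 0 | 14.3% | 7.3% |
| 0.5 | 12.5% | 6.3% |
| 0.9 | 8.4% | 4.2% |
| One marker only | 5% | 2.5% |

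If all three are kept at 0.05/3 = 0.0167 each, the error is at most 5%. Power per marker at d = 0.5 and 65 per arm then falls from 80.8% to 66.4%.

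**Reading B: one per-patient responder rule, tested once.** Type I error is 5%. The cost lies in the responder rate and in power.

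*No-change responder rate.* The within-person CV is not in the protocol; 20% and 30% are assumed. The SD of the log change is √(2 ln(1 + CV²)), which is 0.280 and 0.415. A 25% fall is ln 0.75 = −0.288 on the log scale, so z = −1.03 and −0.69. The chance of such a fall in one marker with no true change is therefore 15% and 24%. For any of three markers it is 31% and 45% at correlation 0.5, and 22% and 33% at 0.9.

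*Power.* Assume a shift of d = 0.5 (in SDs of the log change) in all three markers and 65 per arm, and compare two proportions by the normal approximation. Example for C16 alone at CV 20%:

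- Responder rates: 15.2% against 29.9%, a difference of 0.147.
- Null SE 0.073, alternative SE 0.072.
- (0.147 − 1.96 × 0.073) / 0.072 ≈ 0.04, so power is about 52%.

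| CV | Correlation | C16 responder | Any-of-three responder |
|---|---|---|---|
| 20% | 0.5 | 52% | 71% |
| 20% | 0.9 | 52% | 59% |
| 30% | 0.5 | 58% | 72% |
| 30% | 0.9 | 58% | 63% |

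The choice of approximation moves these by about one point, so the ranges are 51-58% and 59-73%. If only C16 moves, the any-of-three rule has about 19-25% power. A continuous comparison of log C16 change at the same d = 0.5 has 80.8%.

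**The case against.** The strongest reply is that no section calls for three separate tests. The percentage thresholds in section 2.4.a can be read as patient-level rules, and under that reading there is one test and no inflation. This stands. A reader might infer that the *or* wording by itself means three chances at 5%, but the protocol does not settle that, so the 8.4-14.3% range is conditional on Reading A.

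Three other inferences are tempting and also go too far.

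- **That C14 and C18 go unmeasured.** The assay note under Table 3 covers several chain lengths, so they can be available. The conflict is over which analyte defines the endpoint.
- **That the *or* rule dilutes a real effect under Reading B.** Hypothesis 2 predicts a fall in the class. If all three markers shift together, any-of-three has more power than a C16 responder rule (59-73% against 51-58%). The loss appears when not all markers move.
- **That the liver-enzyme endpoint has the same fault.** It reads "Reduction in any abnormally raised liver enzymes (GGT, ALT, AST) by more than 30" per cent, so a patient contributes only enzymes that are abnormally raised. It is a different rule, no calculation supports changing it, and choosing one enzyme would be a preference.

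It is also fair to say that this is one of five secondary endpoints, that the markers are plausibly positively correlated (so 14.3% is near the upper end), and that a SAP, which is not shown, commonly carries secondary multiplicity. But the disagreement between section 2.4.a and Table 1 is in the protocol's own text and is not a detail left for later. A pre-specified sum of chain lengths would also suit a class hypothesis; C16 is preferred because Table 1 already singles it out.

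**Conclusion.** The point holds as an inconsistent and incompletely fixed success rule for a secondary endpoint. The disagreement between the passages rests on the text alone and needs no assumption.

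Its statistical size depends on the reading. With separate tests the false-positive rate is 14.3%, 12.5% or 8.4% at correlation 0, 0.5 or 0.9. With one responder rule it is 5%, and the price is a no-change responder rate of 31-45% in place of 15-24% (correlation 0.5) and power below a continuous analysis. The correlations, the CVs of 20-30% and d = 0.5 for these markers are assumptions.

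Under either reading, one named marker analysed on a continuous scale does better at d = 0.5: 5% error and about 81% power at 65 per arm. HbA1c, its significance level and the sample size are not touched, so this is a change that should be made but does not threaten the trial's main conclusion. The liver-enzyme endpoint needs no change on this ground.

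**What to change.** In section 2.4.a, make C16, the marker in Table 1, the single endpoint for Hypothesis 2. Define its analysis as the between-arm difference in the change of log C16 from week 0 to week 24. Report C14 and C18 descriptively. Align section 2.4.a, Table 1 footnote b, and Table 3 with its assay note, so that all name the same endpoint analyte.

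If all three markers must stay as separate tests, adjust for three (for example 0.0167 each) and accept the lower power per marker shown above.

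No additional samples or visits are needed, but this is slightly more than an edit of wording: the 25% threshold gives way to a continuous comparison and the time point is fixed. The real downside is that an isolated effect on C14 or C18 can no longer be claimed as meeting the endpoint.

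### Secondary endpoint 4 counts a 15 mL/min/1.73m² fall in eGFR, which is a loss of kidney function, as efficacy

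*Protocol*

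**What the plan says.** Section 2.4 splits its endpoints into sub-section a, "End Points – Efficacy", and sub-section b for safety. Item 4 of the secondary list in sub-section a reads "Reduction in calculated eGFR by 15 mL/min"/1.73m². It is not limited to any subgroup or baseline eGFR, and no reason is given for the direction.

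The next item, also renal, reads "Reduction in urine ACR in macroalbuminuric patients (urine ACR > 300 mg/g) of at least 48" percent. The renal objective in section 2.3 is "To study the effect of drinking oxygen-enriched ELO water on diabetic nephropathy". Hypothesis 3 in section 2.1 says that ELO water "is able to improve albuminuria in Type 2 diabetes patients better than hydration with regular water". The background in section 1 reports a review finding that "increasing water intake may have a beneficial effect on renal function in patients with all forms of chronic kidney disease", and says that good hydration "could help ameliorate diabetic nephropathy".

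Table 1 and Table 3 schedule serum creatinine and calculated eGFR at weeks 0, 6, 12 and 24.

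**The concern.** HbA1c, fasting glucose, acylcarnitine, raised liver enzymes and urine ACR all improve when they fall. eGFR improves when it rises. The same word, reduction, has been applied to all of them, so item 4 points the opposite way from the rest of the list.

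If the endpoint is followed as written, harm to the kidney from the water would be reported as a benefit, and preserved kidney function as a failure. No other endpoint would report the loss as harm: the safety list in section 2.4.b contains only statements on delivery and product approval, and section 9.3 provides for no data safety monitoring board. Section 9.1 does use laboratory results to follow the wellbeing of individual patients, but that is not a comparison between arms.

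**Working it through.** The protocol gives no calculation behind item 4, so the check is one of direction.

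**1. What item 4 scores.** Take a baseline of 60 mL/min/1.73m² for illustration only, since the protocol gives no expected baseline. Read the threshold as 15 or more.

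| eGFR, baseline to week 24 | Change | Kidney function | Item 4 as written |
| --- | --- | --- | --- |
| 60 to 45 | 45 − 60 = −15 | worse | met |
| 60 to 60 | 60 − 60 = 0 | preserved | not met |
| 60 to 75 | 75 − 60 = +15 | better | not met |

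By definition, everyone who meets the endpoint has lost kidney function. If the proportions meeting it are compared between arms, the arm with the higher proportion is called the better one, and that is the arm with more renal loss.

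**2. Against the rest of the list.** The primary endpoint and secondary items 1, 2, 3 and 5 are all reductions that mean improvement. Item 4 alone is a reduction that means deterioration.

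**3. Against the hypothesis and rationale.** Hypothesis 3 predicts an improvement, stated for albuminuria. The background presents extra water as potentially good for renal function. Neither treats a lower eGFR as a goal.

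**4. Could a fall be the intended benefit?** Relief of hyperfiltration would be the argument, but the protocol never mentions it. Where a reduction is good only in patients with an abnormal value, the list says so: item 3 is limited to raised enzymes and item 5 to ACR above 300 mg/g. Item 4 has no such limit. Eligibility (sections 3.3 and 3.4) sets no eGFR range; the nearest restriction is the exclusion of conditions needing fluid restriction, for which section 1.1.c gives renal failure as an example.

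**5. Reach.** There are two renal endpoints. Item 5 covers only macroalbuminuric patients, so item 4 is the only one that applies to all 150. The sample size in section 11.1 rests on a generic Cohen's d of 0.5 and not on eGFR, so correcting item 4 changes neither the 65 per arm required nor the 75 per arm recruited.

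**The case against.** The strongest counter-argument is that item 4 may be a harm threshold put in the wrong list. The parent section is titled as covering both risks and benefits, and the safety list contains no measured outcome. On that reading the direction is right and the classification is wrong. This cannot be excluded, and the document does not reveal what was intended. The text still needs correcting on either reading, because item 4 stands under the efficacy sub-heading.

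Three further points limit the claim:

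- The support is partly indirect. The objective in section 2.3 is neutral in direction, the background sentence on nephropathy concerns hydration, which both arms receive, and Hypothesis 3 names albuminuria rather than eGFR. The contradiction therefore comes from the efficacy heading, the neighbouring items and the general rationale.
- The renal objective is not wholly lost. Urine ACR also serves it and points the right way.
- Section 11.2 plans two-tailed tests and mixed models for repeated measures. A between-arm analysis of eGFR as a continuous variable would keep its true sign. However, the section does not say that eGFR will be analysed in that form, and a two-tailed test does not settle which direction is called efficacy. The endpoint definition does that.

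The proposed change also goes further than reversing a sign. Turning the item into a rise of 15 would still score preserved function as failure, and the protocol gives no basis for a rise of that size. A signed change avoids both problems.

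**Conclusion.** The concern holds. As written, item 4 is an efficacy endpoint that is met only by losing kidney function, and no other part of the protocol repairs or explains it. The reversal is complete for this endpoint. That follows from the definition and is not an estimate of how many patients would be affected. The conclusion rests on reading the efficacy sub-heading at face value and on taking a lower eGFR as worse function, in the absence of any stated hyperfiltration rationale.

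The consequence is limited to one of five secondary endpoints. It should nevertheless be corrected before any data are compared by arm, because a stated rule that presents harm as benefit gives a wrong answer when followed, and choosing the direction after seeing results would be post hoc.

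**What to change.** In section 2.4.a, replace item 4 with: change in eGFR (mL/min/1.73m²) from baseline to week 24, compared as ELO minus placebo, a positive difference favouring ELO.

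In section 2.4.b, add: number and proportion of patients in each arm whose eGFR has fallen by 15 mL/min/1.73m² or more from baseline at week 24. This keeps the protocol's own threshold and covers the possibility that item 4 was meant as a harm measure. The sponsor should confirm which was intended.

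Both changes should be made before any analysis by arm, including the month 3 analysis planned in section 11.2. The cost is a line or two of wording in a protocol amendment. No extra visit, sample or patient is needed.
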